### 9.3 POPULATIONS FOR ANALYSES

Primary analyses will be performed using data from all randomized participants (ITT population). Additional assessments of primary endpoints will be completed for study completers (baseline and follow-up assessments) and on participants completing at least 50% of the assigned intervention tasks (i.e. lessons and webinars).

### 9.4 STATISTICAL ANALYSES

#### 9.4.1 GENERAL APPROACH

Data analyses will be performed using SAS statistical software (Version 9.4 or higher, Cary, NC). Baseline descriptive characteristics will be summarized globally, and by arm, using frequencies and percentages for categorical variables, and means and standard deviations (or median [Q1, Q3] for non-symmetric data) for inherently quantitative variables. Prior to conducting data analyses, we will audit the data for completeness and quality, including missing data. We will evaluate distributions to ensure that they meet the assumptions of planned analyses (see 9.4.2 and 9.4.3), including the detection of outliers.

#### 9.4.2 ANALYSIS OF THE PRIMARY ENDPOINT(S)

Our primary analyses will involve testing change in the total score from CD-RISC between SMART and control groups at 3 months. Using maximum likelihood methods, we will use multi-level linear mixed models (PROC MIXED) that include random effect for cluster to account for covariance between participants within the same center as well as fixed effects for time (0, 3, 9, 15 months), trial arm (SMART or matched attention control), time\*arm interaction. To assess the primary endpoint from this mixed model we will include a contrast statement to calculate mean and 95% confidence intervals to estimate change for our primary outcome from baseline to 3- (primary endpoint), 9-, and 15-months (secondary endpoints). A proper error covariance structure will be chosen based on model fit indicated by model likelihood, Akaike Information Criterion and Bayesian Information Criterion. Residuals will be examined to check the assumptions of models. To further explore the effect of the intervention, sensitivity analyses will be conducted that adjust for baseline variables distributed differently between groups and to examine completers only. Similar analyses will be completed for secondary outcomes. Baseline variables including center and worker demographics will be included as covariates to assess their potential moderating effect

All analyses will be conducted using the intention-to-treat principle, in which all available data on all randomized participants are included. This approach minimizes bias if individuals drop out of the trial for different reasons. Every effort will be made to obtain follow-up data on all participants randomized, whether or not they follow their assigned treatment. Our maximum likelihood approach assumes that any missing outcome data are missing at random (i.e., missing data including that due to drop-out can be dependent on any previously observed outcomes or treatment assignment). With this approach, we use all data that have been collected without regard to whether data are missing for a participant at another visit, including drop-out, and without explicit imputation of missing data. If the combined rate of missingness on variables is above 5%, we will impute missing endpoint data using multiple imputation

techniques and will assess the sensitivity of our results to various assumptions of missing data patterns. The methodological literature currently recommends an inclusive analysis strategy that incorporates auxiliary variables into the missing data handling procedures because this approach can make the missing at random assumption more plausible and can improve statistical power. All outcome variables and auxiliary variables (i.e., measured worker and center characteristics) will be incorporated into the imputation process.

---

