### 9.2 SAMPLE SIZE DETERMINATION

The study is powered to detect a between group difference (Resilience group vs attention control) of overall resilience assets and resources as assessed with the CD-RISC (primary outcome). An effect size of at least 0.35 is expected, representing a clinical meaningful difference and a conservative estimate based off the SMART resilience program's well-documented efficacy to facilitate change across several mental health related outcomes (with effect sizes ranging from 0.3 to 1.1). Based on previous work we anticipate that, on average, about 8 workers will participate at each childcare center. Since this is a cluster randomized design, we assume that there will be an inherent ICC within centers. The ICCs observed in our previous work assessing childcare worker health outcomes ranged from 0.00 to 0.13.

*Statistical power table* describes the power for a range of ICCs, number of centers per arm, and effect sizes. Given these assumptions, a sample size of 80 centers (40 per arm), with an

| Statistical Power |             |      |      |      |      |
|-------------------|-------------|------|------|------|------|
| Centers per arm   | Effect Size | ICC  |      |      |      |
|                   |             | 0.00 | 0.03 | 0.10 | 0.13 |
| 30                | 0.30        | 0.91 | 0.84 | 0.67 | 0.60 |
| 30                | 0.35        | 0.97 | 0.93 | 0.80 | 0.73 |
| 30                | 0.40        | 0.99 | 0.98 | 0.89 | 0.84 |
| 35                | 0.30        | 0.94 | 0.89 | 0.73 | 0.67 |
| 35                | 0.35        | 0.99 | 0.96 | 0.85 | 0.80 |
| 35                | 0.40        | 1.00 | 0.99 | 0.93 | 0.89 |
| 40                | 0.30        | 0.97 | 0.92 | 0.79 | 0.73 |
| 40                | 0.35        | 0.99 | 0.98 | 0.90 | 0.85 |
| 40                | 0.40        | 1.00 | 0.99 | 0.96 | 0.93 |

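### Section 9.4.2 names one center random effect and no center-by-time term; read as an intercept, it drops out of the baseline-to-3-month contrast, so the primary test is anti-conservative if change varies by center

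*Protocol*

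**What the plan says.** Section 9.4.2 describes multi-level linear mixed models, fitted in PROC MIXED by maximum likelihood, which "include random effect for cluster to account for covariance between participants within the same center". The fixed effects are time (four visits), arm and their interaction. Contrasts estimate change from baseline to 3 months (primary) and to 9 and 15 months (secondary). For the remaining covariance, "A proper error covariance structure will be chosen based on model fit indicated by model likelihood, Akaike Information Criterion and Bayesian Information Criterion". The section names no center-by-time effect, no robust variance and no degrees-of-freedom method.

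Section 4.1 makes the center the unit of randomization. Section 9.2 sizes the trial for clustering: "Since this is a cluster randomized design, we assume that there will be an inherent ICC within centers". It uses an ICC of about 0.10, an average of 8 workers per center and 40 centers per arm, and reports ICCs of 0.00 to 0.13 from earlier work on childcare workers' health outcomes.

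**The concern.** Section 9.4.2 gives the random effect the job of handling covariance between coworkers. A center intercept does that for scores at a single visit. The primary endpoint is a difference between two visits, and a center effect of the same size at both visits subtracts out. What would protect the primary test is a center component that differs between visits, and none is named. The participant-level error covariance does not supply one, because it links a worker's visits to each other and not one worker to another.

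If centers differ in how much their staff change, the standard error of the primary contrast is too small, the confidence interval too narrow and the p-value too low. The 9- and 15-month contrasts share the problem, as do secondary endpoints that Section 9.4.3 refers to the same procedures. The sizing and the test also part company: Section 9.2 charges the comparison a design effect that the Section 9.4.2 test, on this reading, does not contain.

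**Working it through.** **Inputs.** From Section 9.2: 40 centers per arm, m = 8 workers per center, ICC about 0.10 (range 0.00 to 0.13), effect size 0.35, alpha 0.05, power 90%. From Section 9.4.2: the model and contrast. Assumed: a two-sided test and the ICC of change, neither of which is stated.

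**The plan's own power figure.** Design effect = 1 + (8 − 1) × 0.10 = 1.70. Effective number per arm = 320 / 1.70 = 188.2. Power is 0.924 by the normal approximation and 0.918 by the noncentral t with 78 df, against a stated 0.90. All 36 table cells come within 0.02 if center size has a coefficient of variation of about 0.4 to 0.5, which the protocol does not state. So Section 9.2 does charge the comparison for clustering.

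**Cancellation.** Write the score of worker i in center j at visit t as fixed effects + u_j + e_ijt. The change from 0 to 3 months is fixed effects + (e_ij3 − e_ij0), and u_j is gone. In matrix terms, with contrast c = (−1, 1, 0, 0) and intercept variance g, the center contribution is c′(g·11′)c = 0.

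**Consequence.** If change scores have ICC ρ_D within centers, the true variance of the contrast is 1 + (m − 1)ρ_D = 1 + 7ρ_D times the model-based one. The actual error of the nominal 5% test is 2 × [1 − Φ(1.96 / √(1 + 7ρ_D))].

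| ICC of change | Variance ratio | True SE / reported SE | Actual error |
|---|---|---|---|
| 0.00 | 1.00 | 1.00 | 5.0% |
| 0.03 | 1.21 | 1.10 | 7.5% |
| 0.05 | 1.35 | 1.16 | 9.2% |
| 0.10 | 1.70 | 1.30 | 13.3% |
| 0.13 | 1.91 | 1.38 | 15.6% |

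At 0.10 a nominal 95% interval covers about 87% (100 − 13.3). If center sizes vary with a coefficient of variation of 0.45, the variance ratio at 0.10 becomes 1.862 and the error 15.1%.

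**From the ICC at a visit to the ICC of change.** Let ρ be the ICC at a visit, r the correlation over time of the center effects, and w the correlation over time of a worker's deviation from the center. Then ρ_D = ρ(1 − r) / [ρ(1 − r) + (1 − ρ)(1 − w)]. With ρ = 0.10 and an assumed w = 0.6, r = 1 gives 0; r = 0.8 gives 0.02/0.38 = 0.053; r = 0.6 gives 0.04/0.40 = 0.10; r = 0.5 gives 0.05/0.41 = 0.122; r = 0 gives 0.10/0.46 = 0.217.

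**Simulation under no arm effect.** 80 centers of 8, four visits, complete data, maximum likelihood, unstructured participant covariance, ρ = 0.10, w = 0.6, test against 1.96. There were 800 runs for r = 1 and 700 for each other row.

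| r | Formula | Center intercept only | Center-by-time added |
|---|---|---|---|
| 1.0 | 5.0% | 5.5% | 5.4% |
| 0.8 | 9.4% | 8.6% | 4.1% |
| 0.5 | 15.0% | 13.6% | 5.0% |
| 0.0 | 21.7% | 19.4% | 5.9% |

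The Monte Carlo standard error, √(p(1 − p)/700), is about 0.8 points at 5% and 1.5 points at 19.4%. The simulation agrees with the formula to within about that error. It shows no inflation when center effects are stable, and a rate near 5% in every row once center-by-time is added.

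**The case against.** The protocol never says that the center effect is an intercept, that it is constant over time, or that it is the only center-level term. It leaves covariance structure to model fit, and the exact RANDOM statement and degrees of freedom are details that an SAP often settles. That stands as a limit: a reader might infer that the protocol commits to a time-constant effect only, and the text does not go that far. It does not remove the point. The section fixes the software, the random effect, the fixed effects and the contrast, and a single cluster effect in PROC MIXED is ordinarily an intercept. The fit-based choice most naturally concerns repeated measures within a participant.

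A reader might also infer that the error rate exceeds 5% as a matter of course. The protocol does not support that. It gives no ICC of change, its quoted range includes 0.00, and a stable center effect gives no inflation even with an ICC of 0.10 at each visit. Under the assumptions above, an ICC of change of 0.10 needs a center autocorrelation of about 0.6 over three months; at 0.8 the simulated error was 8.6%.

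Nor does the protocol establish that change must cluster. Modules are self-paced, coaching is one-on-one with directors, and webinars are not said to run center by center (Section 6.1). Against that, directors are coached before each module, the protocol expects more talk about health within centers (Section 2.3.3), and it hypothesizes improved organizational support (Section 9.1). Clustering of change is plausible, but its size is unknown.

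Finally, cancellation is exact only with complete data. Section 9.2 allows for 15% loss at 3 months, so the figures are then approximate.

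**Conclusion.** The point holds in conditional form. On the ordinary reading of Section 9.4.2, the named center effect does not protect the primary contrast, or those at 9 and 15 months, against center-level variation in change. If such variation exists, the nominal 5% test runs at about 7.5% to 15.6% for an ICC of change between 0.03 and 0.13 with 8 workers per center; if there is none, nothing is lost. These figures rest on a two-sided test, equal center sizes, complete data and an ICC of change that the protocol does not give. A primary test in a cluster-randomized trial should not depend on an unstated assumption that this variance is zero, particularly when Section 9.2 plans for clustering.

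A reader might also take the fit-based choice of error covariance as part of the fault. It is not: choosing a participant-level residual structure by stated criteria is conventional, and that choice neither causes the problem nor cures it.

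**What to change.** In Section 9.4.2, add a center-by-time random effect to the center effect, or state an equivalent center-level covariance over visits. State that the contrasts will be tested with center-based degrees of freedom. If Kenward-Roger is chosen, change the estimation from maximum likelihood to REML, for which that method was derived. The AIC/BIC choice of participant-level structure can stay.

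The cost is a few words in the protocol, one extra term in the model, possibly a change of estimation method, and no new data. The confidence interval becomes wider when change clusters by center, by about 1.30 times at an ICC of change of 0.10. The simulation supports the center-by-time term under maximum likelihood with a normal reference; it did not test REML with Kenward-Roger.

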#### **Randomization.**

Centers will serve as the unit of randomization. Soon after baseline testing, each center will be randomized to either the Resilience program or the Physical Activity program. Randomization tables with a permuted block approach (block sizes of 2-4) will be used to ensure equal distribution between arms throughout the randomization period. Intervention assignment will only be known to the project manager and the behavioral health counselor delivering the intervention. Investigators and data collectors will be kept blinded.

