## 8 STUDY ASSESSMENTS AND PROCEDURES

### 8.1 ENDPOINT AND OTHER NON-SAFETY ASSESSMENTS

As required by the grant mechanism all recruitment, screening, and measurement procedures must take place virtually or over the phone. No in-person contact with participants is allowed. For screening and recruitment, we will first identify potential childcare centers using the North Carolina Division of Child Development and Early Education website, a publicly accessible database of all licensed childcare centers in North Carolina. Leveraging our existing relationships with state-wide agencies, we will engage community partners (e.g., Smart Start programs, Partnership for Children, Go NAPSACC technical assistants in relevant counties), to provide a soft introduction to the research study that endorses participation (e.g., email announcements, flyer, regular communication channels).

The research team then follows up with direct contacts using multiple communication channels (i.e., email invitation and phone calls) to recruit centers, directors, and staff. Contacts always start with the center director/owner to confirm interest and eligibility. Centers must have at least 8 childcare workers to be eligible. Once a director is screened and agrees to participate, the research team works with the director to engage and recruit center staff (e.g., email/post a flyer, talk virtually at a staff meeting). Center staff will fill out an eligibility screener and be given multiple opportunities to learn more about the project before agreeing to participate. A complete list of inclusion and exclusion criteria can be found in sections 5.1 and 5.2.

After screening and verbal agreement, directors and staff will be sent informed consent and a demographic questionnaire. All measures will be collected through the Qualtrics online survey platform. After consent is complete a link to the full baseline survey will be sent to each participant. If the baseline questionnaire is not completed within 4-days, study staff will attempt to call or text participants to encourage they finish surveys. Staff with incomplete consent, demographics, or primary outcome measures will not be randomized. During each follow-up measurement period (3-, 9-, and 15-months), participants will be sent a link to a survey and reminders for 7 days (1 per day until survey completed). If a survey is not completed within 4-days, study staff will attempt to contact a participant by phone or text.

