#### 9.4.5 BASELINE DESCRIPTIVE STATISTICS

While randomization should be sufficient to balance baseline characteristics of the staff and directors recruited to each arm, we will compare age, race/ethnicity, weight, income, education, years working at ECE center, center size, and center cost (per week) between study arms using simple mean or frequency comparisons. If group differences are deemed statistically significant and clinically meaningful, we will fit models with and without covariates for assessment.

---

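### The primary model leaves the arms free to differ at a pre-randomization baseline, so it tests unadjusted change and loses precision that baseline adjustment would keep

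*Protocol*

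**What the plan says.** Section 9.4.2 fixes the primary model. It has "fixed effects for time (0, 3, 9, 15 months), trial arm (SMART or matched attention control" and the time-by-arm interaction, and it will "include random effect for cluster to account for covariance between participants within the same center". Contrasts from this model are used "to estimate change for our primary outcome from baseline to 3- (primary endpoint), 9-, and 15-months (secondary endpoints". Baseline CD-RISC is therefore one level of the outcome. It is not a covariate, and nothing sets the arms equal at month 0.

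Two other places establish what baseline is. Section 4.1 (Randomization) states: "Soon after baseline testing, each center will be randomized to either the Resilience program or the Physical Activity program". Section 8.1 states: "Staff with incomplete consent, demographics, or primary outcome measures will not be randomized".

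On other covariates, section 9.4.2 says "sensitivity analyses will be conducted that adjust for baseline variables distributed differently between groups and to examine completers only". Section 9.4.5 lists staff and center characteristics to be compared between arms by plain comparisons of means or frequencies, and adds: "If group differences are deemed statistically significant and clinically meaningful, we will fit models with and without covariates for assessment".

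**The concern.** Baseline precedes randomization, so the two arms share one true baseline mean, and any observed difference is chance. A model with a free arm effect at month 0 subtracts that chance difference at full weight. A baseline-adjusted estimate subtracts only the part that predicts the 3-month score. The second is never less precise, and it needs no data beyond what section 8.1 already requires. At stake is precision on the primary endpoint in a trial limited to 80 centers.

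A smaller point concerns section 9.4.5. Under randomization, a significance test of a baseline difference tests a hypothesis known to be true. It is a poor rule for deciding whether adjusted models are fitted, because it responds to chance and not to how strongly a variable predicts the outcome.

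**Working it through.** **Inputs from the protocol (section 9.2):** 40 centers per arm, 8 workers per center on average, ICC about 0.10, effect size 0.35, α = 0.05 (taken as two-sided), stated power 90%; 84% after losing 12 centers and 82% after losing 16.

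**Inputs assumed:** the correlations over time, which the protocol does not give, and a coefficient of variation (CV) of center size of 0.5.

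**Step 1: reproduce the stated power.** With 320 workers per arm, power = Φ(0.35·√(160/DE) − 1.96).
- Equal center sizes: DE = 1 + 7 × 0.10 = 1.70, power 0.924 (0.918 with a t distribution on 78 df).
- Center sizes with CV 0.5: DE = 1 + (1.25 × 8 − 1) × 0.10 = 1.90, power 0.895. The same DE gives 0.84 with 34 centers per arm and 0.82 with 32, matching the stated 84% and 82%.

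The stated figures reproduce; DE = 1.90 is used for power below.

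**Step 2: compare the two estimators.** In units of the variance of a center mean, unadjusted change has variance 2(1−r) and the baseline-adjusted score has 1−r². Adjusted over unadjusted = (1+r)/2, so the loss is (1−r)/2.

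**Step 3: find r for center means.** r = [m·ICC·CAC + (1−ICC)·IAC] / [1 + (m−1)·ICC], where CAC and IAC are the center-level and worker-level correlations over time. With m = 8 and ICC = 0.10 this is r = (0.8·CAC + 0.9·IAC)/1.7.

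| CAC | IAC 0.4: r, loss | IAC 0.7: r, loss |
|---|---|---|
| 1.0 | 0.682, 16% | 0.841, 8% |
| 0.8 | 0.588, 21% | 0.747, 13% |
| 0.6 | 0.494, 25% | 0.653, 17% |

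The single random center effect named in section 9.4.2 corresponds to CAC = 1.0. A generalized least squares calculation with all four time points agrees: at CAC 1.0 and IAC 0.5 the variances are 0.005625 (planned) and 0.004881 (constrained), a loss of 13%, and the formula gives (1 − 0.735)/2 = 13%.

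**Step 4: effect on power, if 0.35 is in SD units of the score.** Power = Φ(0.35·√(160/(1.90·V)) − 1.96), with V = 2(1−r) as planned and V = 1−r² after the change.
- r = 0.4: V = 1.20 and 0.84, power 83% and 94%.
- r = 0.5: V = 1.00 and 0.75, power 90% and 96%.
- r = 0.7: V = 0.60 and 0.51, power 99% and 99%.

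With 34 centers per arm, 160 becomes 136: 77% and 90% at r = 0.4, 84% and 93% at r = 0.5.

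**The case against.** The strongest defense is that the specification is a standard repeated-measures model, that its contrast is unbiased under randomization, and that no figure in the protocol is shown to be wrong. All of that stands. This is a matter of efficiency, not of validity. Several stronger readings are tempting, and the documents do not support them.

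- **A fixed loss of 15% to 30%.** A reader might put r = 0.4 to 0.7 straight into (1−r)/2. But r is the correlation of center means. With ICC 0.10 and a stable center effect, it exceeds the worker-level correlation, and the loss is about half as large. No correlation is stated, so only a range is defensible.
- **The 90% power is overstated.** Section 9.2 does not say which SD the 0.35 refers to. If it is the SD of change, 90% already describes the planned analysis. If it is the SD of the score, planned power falls below 90% only when r is below about 0.5. In the table that happens only at CAC 0.6 with IAC 0.4.
- **Covariates enter only through significance tests.** Section 9.4.2 also says "Baseline variables including center and worker demographics will be included as covariates to assess their potential moderating effect", and it puts worker and center characteristics into the imputation model; neither depends on a test. Section 9.4.5 requires clinical meaning as well as significance.
- **The baseline tests ignore clustering, and center variables will be flagged far too often.** The unit of comparison is not stated. Center size and cost compared across 80 centers would keep the nominal error rate.
- **The rule allows a choice between two results.** Section 9.4.2 has no covariates in the primary model and labels the adjustment for imbalance a sensitivity analysis.

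A named covariate list may also sit in the SAP, which is not shown, so its absence from the protocol is no finding.

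**Conclusion.** The point holds as an efficiency weakness in what section 9.4.2 states. With a pre-randomization, complete baseline, the planned contrast gives up (1−r)/2 of the precision available. At the planning ICC of 0.10 with 8 workers per center and an assumed worker-level correlation of 0.4 to 0.7, that is about 8% to 16% with center effects constant over time, and up to about 25% with a center correlation over time of 0.6. On 80 centers, 8% is worth about 6 centers (0.079 × 80), 16% about 13 (0.159 × 80) and 25% about 20 (0.253 × 80).

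This rests on the assumed correlations, on complete data, on equal center sizes in the formula for r, and on adjustment that acts at the level of center means. The power comparison also rests on 0.35 being in SD units of the score and on DE = 1.90. The direction does not depend on these values: the loss is positive for any r below 1. The significance trigger in section 9.4.5 is a secondary weakness that leaves the primary estimate untouched.

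**What to change.** In section 9.4.2, make the primary analysis one of the following:

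- the same mixed model with a common baseline mean: time as a four-level factor plus arm-by-time terms at 3, 9 and 15 months, without an arm effect at month 0; or
- the 3-month CD-RISC score adjusted for baseline CD-RISC, with the center random effect kept.

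The first stays closest to the present text, because it keeps every randomized participant's data and yields the 9- and 15-month contrasts from the same fit.

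In section 9.4.5, report baseline characteristics by arm descriptively, and remove statistical significance as the condition for fitting covariate-adjusted models.

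The cost is a few lines of protocol text and a small change to the SAS code. No new data and no change in sample size are needed. The change should be made before outcome data by arm are seen.
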